### **Record Retention and Archiving**

In compliance with the ICH/GCP guidelines, regulations and in accordance with the University of Nottingham Code of Research Conduct and Research Ethics, the Chief or local Principal Investigator will maintain all records and documents regarding the conduct of the study. These will be retained for at least seven years or for longer if required. If the responsible investigator is no longer able to maintain the study records, a second person will be nominated to take over this responsibility.

The study master file held by the Chief Investigator on behalf of the Sponsor shall be finally archived at secure archive facilities at the University of Nottingham. This archive shall include study databases and associated meta-data encryption codes.

### **Discontinuation of the Trial by the Sponsor**

The Sponsor reserves the right to discontinue this study at any time for failure to meet expected enrolment goals, for safety or any other administrative reasons. The Sponsor shall take advice as appropriate in making this decision.

### **PUBLICATION AND DISSEMINATION POLICY**

The study results will be submitted to Arthritis Research UK, regulatory authorities, and peer-reviewed journals for publication. In addition, the results will be presented at national and international conferences. Study participants' identity will not be disclosed when publishing the results. Study participants will also be informed of the results if requested.

### **USER AND PUBLIC INVOLVEMENT**

On the PPI representative meeting of 14/12/2015, seven volunteers suffering from chronic arthritis pain were asked about the relevance of studying sleep in the context of OA pain. They all were very supportive of studying and understanding sleep patterns. They viewed

actigraphy as a good non-invasive alternative to polysomnography and saw no problem with using the device for 6 weeks.

On 17/05/2017 6 representatives from the PPI MSK group were asked about exercise interventions and were all supportive of this. They were also asked about the extraction of synovial fluid from their joints. Five out of six said they would not have a problem with this if it was performed by a specialist using ultrasound to guide the needle, which is why this is an optional part of the protocol.

The latest versions of the participant facing documentation (PIS, consent form, invitation letter and flyer) has all been forwarded to three PPI representatives who have reviewed and commented on it.

## **STUDY FINANCES**

### **Funding source**

This study is part-funded by the Arthritis Research UK Pain Centre (University of Nottingham) and part-funded by MRC Arthritis Research UK Centre for MSK Ageing Research, School of Life Sciences, University of Nottingham.

### **Participant stipends and payments**

Participants will not be paid to participate in the study. However, all travel expenses to and from Academic Rheumatology, Clinical Sciences Building, Nottingham City Hospital will be covered.

#### **Trial Registration number:**

NCT03545048

#### **SAP version:**

V1

#### **Protocol Version:**

V1 published and link:

<https://bmjopen.bmj.com/content/9/10/e030564>

#### **SAP Revisions:**

Not applicable

### **Section 2: Introduction**

#### **Background**

Osteoarthritis is the most common cause of disability in the elderly population and most individuals suffering from osteoarthritis is managed in the primary care setting (1). Knee osteoarthritis is the most common form of arthritis in the world (2). The rate of knee arthritis is as high as that of cardiac disease and is the most common problem in the individuals over the age of 65 (3). In the United Kingdom, 10% of individuals between the ages of 65 and 74 consult their general practitioners about osteoarthritis every year (4). 4% of general population see their general practitioners as a result of knee osteoarthritis, and half of them (2%) consult their general practitioner for the first time or with an acute flare of knee arthritis (1).

According to national and international guidelines, the first line of treatment for osteoarthritis pain (OA) is non-surgical; exercise, information and, in relevant cases, weight loss (5-9). There is sufficient evidence for the effectiveness of exercises in the management of knee osteoarthritis and to improve the functional capacity of these individuals to cope better with the activities of daily living (10-24). In fact, one study reported a slow-down of progressive radiographic changes of knee OA as a result of

strengthening exercises (25). There is a significant disparity on the effectiveness of different types of exercises for the knee osteoarthritis, and a combination of open and closed isotonic exercises are recommended knee osteoarthritis (26) with the exception to those individuals who find these exercises difficult and painful. In such groups, isometric exercises of knee muscles should be considered (26). In an attempt to manage the knee osteoarthritis, one can exacerbate the symptoms of knee arthritis by following ineffective or unsafe exercises leading to poor prognosis and poor adherence to these exercises (27), hence the need to choose the exercises carefully.

There are no standardised exercise programs for knee OA in the United Kingdom. Arthritis Research UK (ARUK) recommend knee exercises for knee pain which is a generic term and covers soft tissue injuries (28). These exercises are normally recommended by the general practitioners as the first line of protocol when they consult someone with the knee pain. If these exercises fail to make remarkable progress, individuals with knee OA are referred to the Physiotherapy department. As there is no standardised protocol, therefore various exercises are given by the physiotherapists which vary in term of contents, intensity and duration. These exercises may help some individuals and may not help others. One example is that a patient may get recommended generic knee exercises which may help individuals with knee OA, however, may flare up the pain in the individuals with the patellofemoral joint syndrome or vice versa. Therefore, there is a need for standardised exercises to address knee OA pain which can ideally be accessed online. The exercise programme which we will use is a part of the web-based exercises which is derived from the Supported Osteoarthritis Self-Management Programme (SOASP) developed in Sweden. In the SOASP, scientific evidence for information and exercise in conjunction with osteoarthritis was put into clinical practice. From 2008 until January 2017, around 75,000 patients had participated the SOASP, 2339 physiotherapists and occupational therapists were educated to hold the Supported Osteoarthritis Self-Management Programme, and today SOASP is offered in 700 units all over Sweden ([https://boa.registercentrum.se/boa-in-english/better-management-of-patients-with-osteoarthritis-boa/p/By\\_o8GxVg](https://boa.registercentrum.se/boa-in-english/better-management-of-patients-with-osteoarthritis-boa/p/By_o8GxVg)). This intervention has been rated as good or as very good by 94% of patients and has an excellent safety profile and acceptability (29).

Because of the high prevalence of knee arthritis, strategies to deliver exercise interventions that are both efficacious and cost-effective becomes a priority. Some of the issues relating to the delivery of exercise interventions for knee OA include compliance, accessibility to clinics for people with mobility problems and cost of delivery of such services. There are previous studies which have assessed the efficacy of home-based exercises and reported good results (12, 14, 30) however very few studies looked at a web-based delivery of exercises on the knee arthritis (31-35). Unfortunately, most of these studies recruited patients with knee pain, and radiographic evidence of knee osteoarthritis was only assessed in a single study (33). Some of these exercises can be used for non-specific knee pain including cases of soft tissue injuries, arthritic knees, patellofemoral syndrome or any other reason for knee pain. However, generalising these results on the group of patients with knee osteoarthritis warrants a risk of increasing their pain just in case that those exercises are strenuous or more demanding. Therefore, there is a need for an exercise programme which is specific for osteoarthritis and economical so individuals can access them in their own homes.

Most individuals lose interest in exercising regularly after they finish with their physiotherapy intervention. There are various reasons for this including adjusting lifestyle to include these exercises, pain during the exercises, lack of motivation and lack of professional to monitor the progress (36-38). So, there is a need for the

intervention which keeps them motivated and improves the compliance and that actually encourages forming a habit of regular exercising.

Knee OA pain is accompanied by a number of additional disturbances that influence the individual's health which we also propose to study in conjunction with pain relief due to exercise. There is well known link between sleep disturbances and chronic pain and both epidemiological studies (39-41) and experimental studies (42-46) have established a link between disturbed sleep and knee OA. These studies confirmed that individuals with OA have the higher suffering from sleep disturbances. Sleep disturbances have been recognised as an important factor in determining the perception of pain in individuals (46). A relationship between sleep disturbances and pain severity in knee OA patients is usually explored, and sleep disturbances such as shortened sleep duration and fragmented sleep (39) have been associated with increased sensitivity to pain in OA patients and consequently with decreased quality of life (41). Therefore, studying the sleeping pattern is highly relevant if we are discussing a successful online exercise programme for knee OA.

Recent epidemiological and clinical studies have also underlined that metabolic syndrome (MetS) has the most significant impact on the initiation and severity of OA (47-51). Metabolic triggered inflammation, also known as meta-inflammation (52) can be a result of abnormalities in body composition, adipokines, cytokines, lipids and vitamin D and has been associated with the pathogenesis of OA (50). However, the intricate links between exercises, sleep, pain, metabolic syndrome and OA are not fully understood. To date, the relationship between improvements in pain due to exercise for pain relief and other changes related to health parameters that have been linked to OA or chronic pain has not been explored. Specifically, the effects of exercise for knee pain relief on sleep, biomarkers of inflammation and insulin resistance is unknown. We aim to study these parameters and establish the link between exercises for knee OA and these parameters.

## **Rational**

This study aims to explore the benefits of internet-based exercises in the patients with knee osteoarthritis to establish if their pain decreases after six weeks. Being a web-based set of activities, it makes it more accessible to the patients living in rural areas or who have difficulty assessing a clinic and should make it more cost-effective and by cutting down the traveling time and freeing up the time of the physiotherapists. Another reason is to establish if we can have a standardised intervention for knee OA which keeps the individuals motivated, and they can manage their pain. Lastly, we will endeavour to explore the complicated relationship between chronic pain, sleep, biomarkers of inflammation and knee osteoarthritis. Our study is different from the other studies as there is not a single study (to our knowledge) which has studied web-based intervention on United Kingdom population of knee osteoarthritis. Furthermore, we will endeavour to recruit only those individuals who have radiographic evidence of knee osteoarthritis. The purpose of these inclusion criteria is to rule out other causes of knee pain such as soft tissue injuries or patellofemoral syndrome and to establish the efficacy of this programme specifically in individuals with knee OA. Therefore, this study can help in generation of recommendations for the clinical setups where most of the symptomatic patients have radiographic evidence of knee osteoarthritis.

## **Objectives**

### **Primary Objective**

The primary aim of the study is to test the effect of an internet-based exercise treatment program on pain, measured on a Numerical Rating Scale (NRS), in knee OA.

### **Secondary Objectives**

Secondary aims of the study are to test the effect of an internet-based exercise treatment program on the following outcomes:

1. Sleep
2. Pain (Pressure pain threshold – PPT, Temporal summation – TS, and conditional pain modulation – CPM)
3. Inflammatory markers on ultrasound (Synovial fluid, synovial hypertrophy and hyper vascularity) (MSK-USS)
4. Muscle Thickness Assessment (MTA) of Vastus Lateralis Oblique (VLO) using MSK-USS
5. Maximum Voluntary Contraction (MVC)- isokinetic contraction of Quadriceps muscle
6. Biomarkers of insulin resistance
7. Physical functioning (Timed up and go test, 30-second sit to stand test)
8. Western Ontario and McMaster Universities Osteoarthritis Index (WOMAC)
9. Pittsburgh Sleep Quality Index (PSQI)
10. General health questionnaire (MSK- HQ)

## **Section 3: Study Methods**

### **Trial Design**

The iBEAT-OA study is a randomised controlled trial in the primary care setting at Nottingham with participants suffering from knee osteoarthritis, 1:1 randomised to web-based exercises or 'usual care'. The study has been approved by the sponsor, Research Ethical committee (REC) and Health Research Authority (HRA).

### **Randomisation**

Participants will undergo computer-generated stratified randomisation by a statistician at Academic Rheumatology using the <https://sealedenvelope.com/> software. Generation of a randomisation schedule will include obtaining the random numbers and assigning random numbers to each subject under the specific treatment conditions. Participants will be equally allocated between treatment arms with at least n=67 per arm. As the online system will be used for randomisation, therefore, code break will be kept online, and the research manager will be responsible for keeping a track of it.

As per cohort multiple randomised controlled trial design mentioned by another study (54), individuals will have an assessment to establish their suitability for this study and once that has been established, we will randomise them into control group and interventional group. At this occasion, individuals will find out that they belong to one group or the other and hence blinding is not possible. Because the lack of masking might affect the motivation of participants randomised into the control arm, individuals in the control arm will be offered access to the web-based exercise programme after the six weeks of the study, if they wish to use it to avoid a placebo effect in this group. Blinding such interventional studies are difficult to achieve as participants will establish as to in which group they are in, however, the examiner will be blinded to the intervention.

## **Sample size**

The sample size calculation is based on a standardised effect size of 0.49, corresponding to a group difference in primary outcome VAS pain of 12 points on a scale of 0-100 (corresponding to a mean difference of 1,2 points on a 1-10 NRS scale). This difference was found in a recent systematic review of 44 high-quality exercise trials for knee OA pain (3537 participants) (56). With this estimated effect, 60 participants in each group is required to achieve 75% power to reject the null hypothesis, with alpha level set to 0.05.

## **Framework**

We hypothesise that i-BEAT OA is superior to “usual care” in primary care setup, in order to decrease pain reported by OA patients.

## **Statistical interim Analyses and stopping guidance**

No interim analysis was planned or performed. As there was no adverse event expected, the trial was not planned to be stopped early.

## **Timing of Final Analysis**

The final analyses will be performed once the trial has stopped and all follow up data has been collected.

## **Timing of outcome assessments**

All outcome variables were collected at baseline, and at follow-up (6 weeks post baseline) in both arms. However, trial was stopped on 19th March 2020 due to the COVID-19 pandemic resulting in having only 105 eligible participants completing both visits.

## **Section 4: Statistical Principles**

### **Confidence intervals and p-values**

Alpha level will be set to 0.05. 95% confidence intervals will be presented (if data allows for parametric analyses).

Adjustments for multiplicity will not be performed. However, primary outcome is defined and will be the main focus for the results interpretation. Remaining analyses will be considered exploratory, and interpreted in light of the general pattern of effects rather than solely based on individual p-values.

Adherence to the i-BEAT OA will be defined as percentage patient completed activities of those distributed by the platform per week. Number of non-compliant participants will be reported.

Analyses will be based on the Intention to treat (ITT) population. Since there are no risks associated with i-BEAT OA, safety analyses will not be performed.

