## **Known Side Effects**

Increased knee, hip or low back pain and one reported case of increased hypertension (106).

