## **ADVERSE EVENTS**

Increase in the knee, hip or back pain are possible adverse effects (106). One case of raised hypertension has been reported by a previous study (111).

Participants will be asked to contact the study site immediately in the event of any serious adverse event. Any adverse event will be recorded and closely monitored until resolution, stabilisation or until it has been shown that the study treatment / intervention is not the cause. Participants can contact physiotherapists (SG) if there is any adverse event. The CI shall be informed immediately of any serious adverse events and shall determine seriousness and causality in conjunction with any treating medical practitioners.

Any serious adverse event (s) related to this study will be recorded and reported to the REC as part of annual reports. Unexpected serious adverse events will be reported within timeframes to the REC and CI will be responsible for all adverse event reporting.

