**Harm**

No risks are associated with the intervention; however we will record any serious adverse event or harms and will report in publications.

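### The SAP waives safety analyses on a no-risk premise that the protocol contradicts, and promises harms reporting without a by-arm summary, denominator or population

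*Combined protocol and SAP*

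**What the plan says.** **SAP.** The waiver is in Section 4, under *Confidence intervals and p-values*: "Since there are no risks associated with i-BEAT OA, safety analyses will not be performed". The *Harm* section repeats the reason and adds a commitment: "No risks are associated with the intervention; however we will record any serious adverse event or harms and will report in publications". The section on interim analyses and stopping says: "As there was no adverse event expected, the trial was not planned to be stopped early".

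**Protocol.** *Known Side Effects*, under the details of the product, reads: "Increased knee, hip or low back pain and one reported case of increased hypertension (106". The *Adverse Events* section says: "Increase in the knee, hip or back pain are possible adverse effects (106". It mentions a case of raised blood pressure again and sets the recording rule: "Any adverse event will be recorded and closely monitored until resolution". That rule covers all adverse events, not only serious ones.

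**SAP background.** Section 2 accepts that badly chosen exercises can make knee arthritis symptoms worse. It also says that carrying results from general knee pain over to knee osteoarthritis "warrants a risk of increasing their pain just in case that those exercises are strenuous or more demanding".

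**Outcomes.** Knee pain on the NRS is primary and WOMAC is secondary. Both are compared between arms as change from baseline, by ANCOVA or, if the distribution requires it, by Mann-Whitney (SAP Section 6).

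**The concern.** The SAP does not merely leave out detail on harms. It states a rule, that there will be no safety analysis, and gives a reason that the protocol contradicts. The protocol obliges the team to collect adverse events, and the SAP then gives those data no planned summary.

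This matters because an increase in pain is the leading listed side effect and pain is also the primary outcome. With no summary fixed in advance, the authors could choose after seeing the data whether to show events by arm, over which participants, and in what detail. The choice of denominator matters too. A participant who left because of a pain flare would be absent from a table restricted to those who completed both visits.

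**Working it through.** The main check is textual. The calculation only shows how much a table could tell us.

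**1. Premise against protocol.**
- *Risk.* SAP Section 4 and the Harm section say there is none. The protocol's Known Side Effects and Adverse Events sections list knee, hip and back pain increases and one case of raised blood pressure.
- *Expectation.* The SAP stopping section says no adverse event was expected. The Adverse Events section names events that may occur.
- *Data.* Section 4 plans no analysis. The Adverse Events section requires any adverse event to be recorded.

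The first two pairs cannot both stand as written. The third leaves required data without a planned summary.

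**2. What the Harm section supplies.** It commits to recording and publication. It does not give arm, denominator, analysis population or form of summary, and no other section does.

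**3. What the efficacy analyses supply.** A mean or median change in NRS or WOMAC shows whether an arm worsened on average. It does not give the number of participants who worsened. Missing values are filled with the group mean (SAP, *Missing data*), so a participant lost after a flare would receive the arm's average. Hip pain, back pain and blood pressure are not in the Section 6 outcome list.

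**4. Precision of a by-arm table.** The documents give no design figure for harms to reproduce. The one sample-size figure, 60 per arm for 75% power at a standardised effect of 0.49, concerns efficacy. It reproduces at 58 per arm by the normal approximation and 59 by the t-test, and this point does not depend on it.

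Inputs: 105 participants completed both visits (SAP, *Timing of outcome assessments*). The split by arm and the number randomised by the stop are not given. I assume an even split, 105/2 = 52.5 per arm. Event rates are not given either, so those below are assumptions.

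- *Zero events in 52.* The one-sided 95% upper bound is 1 − 0.05^(1/n) = 1 − 0.05^(1/52) = 5.6%. With n = 52.5 it is 5.5%, with 60 it is 4.9%, and with the planned 67 it is 4.4%.
- *Risk difference, 5% v 15%.* Half-width = 1.96 × √[(0.05×0.95 + 0.15×0.85)/52.5] = 1.96 × √(0.175/52.5) = 0.113. The interval is 10 ± 11.3 points, about −1 to +21.
- *Power of a two-sided 5% test*, by Φ{(δ − 1.96√(2p̄(1−p̄)/n)) / √[(p₁(1−p₁) + p₂(1−p₂))/n]}, where δ is the difference in rates and p̄ their average: 16% for 5% v 10%, 40% for 5% v 15%, 65% for 5% v 20%, and 83% for 5% v 25%.

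Only large differences would be detected, so a table should describe and not test.

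**The case against.** The strongest reply is that harms reporting is already promised. That is correct. A reader might infer from the waiver that no between-arm comparison of harm will exist, but the Harm section does not support that. Publication of harms is committed, and a split by arm is possible though unspecified.

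Second, the main listed harm is close to the primary outcome. A reader might infer that worsening knee pain would go unreported. It would not: average worsening would appear in the NRS and WOMAC comparisons. What is missing is the count of participants who worsened and the other listed effects.

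Third, a reader might conclude that event counts cannot be compared between arms because only the intervention arm had a programme physiotherapist by chat or phone. The extra contact is real, but the contact route in the Adverse Events section is not arm-specific, and both arms were reassessed at six weeks. Unequal ascertainment is plausible, not shown.

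Fourth, the evidence of risk is modest. The blood pressure effect is one case, which the Adverse Events section credits to a study whose title describes gym and hydrotherapy strengthening. The background warnings concern unsuitable exercises in general, and the SAP describes the Swedish parent programme as having an excellent safety profile. This stands as a reason not to call the programme hazardous. It does not turn low risk into no risk, because the protocol itself lists these effects for this product.

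Finally, the stopping section does not say that there are no risks. It says no adverse event was expected. It conflicts with the protocol in that narrower sense.

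**Conclusion.** The point holds in this form: the waiver and its repeated reason contradict the protocol and fit poorly with the SAP's own background, and the promise to publish harms lacks a by-arm summary, denominator and population. The textual conclusion needs no assumption.

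The primary estimate and its validity are not affected. The documents do not show that the programme is unsafe, or that the publication will claim safety without data.

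The bound of about 5.6% is an illustration. It rests on roughly 52 participants per arm and a hypothetical count of zero. It shows that even a clean record in a trial of this size could not establish the absence of risk, and also that the proposed table will have low precision.

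**What to change.** 1. Delete the no-risk statements and the safety-analysis waiver from SAP Section 4 and the Harm section.
2. Reconcile the sentence on expected adverse events in the stopping section with the protocol's Known Side Effects and Adverse Events sections. This point takes no position on whether any stopping rule was needed.
3. Pre-specify one descriptive table by arm, over all randomised participants: the number with any recorded adverse event, with each protocol-listed event (knee, hip or back pain increase; blood pressure event), and with any serious adverse event. Give 95% confidence intervals and no formal test.
4. Optionally, and as description only, add the proportion per arm whose observed NRS was higher at six weeks than at baseline, with risk difference and 95% confidence interval. Leave imputed values out. A one-point rise may be noise, so it should not be labelled as harm.
5. State as a limitation that events were largely self-reported and that the intervention arm had extra physiotherapist contact. The trial stopped on 19 March 2020 with outcomes already collected, so a new question at the six-week visit is not an option.

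The cost is SAP wording and one table from records that the protocol already required. The downside is one extra table of low precision.
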